### 6.5.3. Survival Follow-Up

Subjects who complete post-treatment follow-up or experience GVHD progression or require a new anti-GVHD therapy should be contacted by telephone, email, or visit at least every 8 weeks (± 7 days) to assess for new GVHD therapy and survival status until death, withdrawal of consent, or the end of the study, whichever occurs first.

## 6.6. Unscheduled Visits

Unscheduled visits may be held at any time at the investigator's discretion, and appropriate clinical and laboratory measurements performed based on AEs or other findings.

# 7. CONDUCT OF STUDY ASSESSMENTS AND PROCEDURES

## 7.1. Administration of Informed Consent Form

Valid informed consent must be obtained from the study subject before conducting any study-specific procedures using an ICF approved by the local ICH/IEC that contains all elements required by ICH E6 and describes the nature, scope, and possible consequences of the study in a form understandable to the study subject. Local and institutional guidelines for ICF content and administration must be followed; the original signed ICF must be retained by the investigator, and a copy of the signed ICF must be provided to the study subject. The informed consent process for each subject must be documented in writing within the subject source documentation. Subjects of childbearing potential must agree to take appropriate measures to avoid pregnancy in order to participate in the study.

## 7.2. Demography and Medical History

### 7.2.1. Demographics and General Medical History

Demographic data and a complete medical and medication history will be collected at screening.

### 7.2.2. Disease Characteristics and Treatment History

A disease-targeted medical and medication history including hematologic malignancy type, current GVHD staging, date of diagnosis, sites of disease, prior anticancer therapy, ablation therapy, prophylaxis therapy, donor type, and other details related to the disease under study will be collected at screening.

## 7.3. Prior and Concomitant Medications

Prior and concomitant medications will be reviewed to determine subject eligibility. All concomitant medications and measures must be recorded in the eCRF, and any medication received or procedure performed within 30 days before randomization and up to the safety follow-up visit will be recorded in the eCRF. The medication record will be maintained after signing the ICF to document concomitant medications, including any changes to the dose or regimen. Concomitant medications include any prescription, over-the-counter, or natural/herbal preparations taken or administered during the study period. Concomitant treatments and/or procedures that are required to manage a subject's medical condition during the study will also be recorded in the eCRF.

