| \| **Primary Objective** \| **Primary Endpoint** \| \| --- \| --- \| \| Compare the efficacy of ruxolitinib in combination with corticosteroids versus corticosteroids in terms of overall response rate (ORR) at Day 28 in subjects with acute graft-versus-host disease (acute GVHD). \| ORR at Day28, defined as the proportion of participants demonstrating a complete response (CR), or partial response (PR) \| \| **Secondary Objective** \| **Secondary Endpoints** \| \| Compare additional response and longer-term efficacy outcomes between treatment cohorts. \| Durable ORR at Day56, defined as the proportion of patients in each arm whose response on day 28 lasts until day 56 after randomization. \| \| DOR at Month 6 for responders will be calculated. The DOR is defined from the time of the onset of response to loss of response. Subjects who died or discontinued will be censored at the  death date or the previous assessment. \| \| Response duration, defined as the time from the first response to the first recurrence/progression of acute GVHD or additional immunosuppressants for GVHD. \| \| NRM at Month 24, defined as the time from enrollment to death due to any causes other than hematologic disease relapse. \| \| Cumulative incidence of relapse (CIR) at Month 24, defined as the proportion of subjects whose underlying hematologic disease relapses. \| \| Disease-free survival (DFS) at Month 24, defined as the time from enrollment to relapse of primary disease or death from any causes, whichever occurred first. \| \| Failure-free survival (FFS) at Month 24, defined as the time from randomization to disease relapse or progression, non-relapse mortality, or the addition of new therapy for acute GVHD. \| \| Overall survival (OS) at Month 24, defined as the time from randomization to death due to any causes. \| \| Assess the incidence and severity of adverse events (AEs) and serious adverse events. \| Clinical safety data (eg, AEs, infections) will be tabulated and listed. \| \| Evaluate the use and discontinuation of  corticosteroids. \| Average and cumulative corticosteroid dose at Days 365; \| \| Evaluate the use and discontinuation of  immunosuppressive medications. \| Proportion of subjects who discontinue immunosuppressive medications at Days365. \| \| Evaluate the incidence of recurrent acute GVHD \| Incidence rate of recurrent acute GVHD through Month 24. \| \| Evaluate the incidence of cGVHD. \| Incidence rate of cGVHD at Month 24. \| \| **Overall Study Design:**  This trial is an open-label, multicenter, prospective randomized two-arm phase II study comparing the efficacy and safety of ruxolitinib plus methylprednisolone (1 mg/kg) vs. methylprednisolone (2 mg/kg) alone. The biomarkers of acute GVHD, such as sST2, sTNFR1, IL-6, IL-8, and REG3α will be tested at acute GVHD onset. Patients with newly diagnosed intermediate-risk or high-risk acute GVHD, as defined by Minnesota acute GVHD risk score and the biomarker score will be included. The treatment efficacy will be evaluated with respect to the level of biomarkers and clinical manifestations. Written informed consent must be obtained from the patients before enrollment in the study. The consent form and related materials are available from the corresponding author on request.  **Study Population:**  Eligible patients with intermediate-risk or high-risk acute GVHD graded according to the modified Glucksberg criteria, Minnesota acute GVHD risk score and the biomarker score and untreated with systemic acute GVHD therapy will be enrolled in this study.  **Key Inclusion Criteria:**   - Male or female, 14 to 65 years old. - Have undergone first allogeneic hematopoietic stem cell transplantation (allo-HSCT) from any donor source using bone marrow, peripheral blood stem cells, or cord blood for hematologic malignancies. - Develop a de novo acute GVHD, defined as intermediate- or high-risk using the Minnesota acute GVHD risk score and MAGIC biomarker algorithm.   **Key Exclusion Criteria:**   - Has received more than one allogeneic stem cell transplant. - Female patients with pregnant or breast-feeding. - Has Acquired Immune Deficiency Syndrome (AIDS), or hepatitis B/C infection, uncontrolled bacterial, fungal, or viral infections. - Allergies to ruxolitinib. - Vital organ dysfunction unrelated to GVHD, including persistent bilirubin abnormalities or severe heart and respiratory diseases. - Relapse of the primary disease or graft rejection after transplantation. - Presence of GVHD overlap syndrome. - Presence of cGVHD or associated clinical signs or DLI-induced acute GVHD or interferon. - Previous history of JAK1/2 inhibitor treatment after transplantation, except JAK inhibitors administered before the transplantation. - absolute neutrophil count (ANC) <0.5×10^9^/L or platelet count (PLT) < 20×10^9^/L - Serum creatinine > 2.0 mg/dL or creatinine clearance < 40 mL/min measured or calculated by Cockroft-Gault equation. - Patients with poor compliance should not be included in the study based on the judgment of the research team, for example if they refused to take medicine at will many times during the previous treatment.   **Study Drug, Dosage, and Mode of Administration:**  **Ruxolitinib plus corticosteroids treatment (ruxolitinib group):**  The initial dose of methylprednisolone is 1 mg/kg/day intravenously given in this arm for at least 7 days. The dosage of ruxolitinib is 5 mg PO QD. CSA will be administered intravenously at a dose of 2 mg/kg twice daily, targeting minimum concentration levels of 150–250 ng/mL. If GVHD response to treatment is assessed as PR/CR at 7 days, methylprednisolone will be tapered, followed by reduction and discontinuation of CSA and then ruxolitinib. The reduction of the methylprednisolone in the ruxolitinib group is gradual, suggesting it be tapered off over 6 weeks as follows: dosage reduced to 0.6 mg/kg/day, 0.4 mg/kg/day, 0.3 mg/kg/day, 0.25 mg/kg/day, and 0.18 mg/kg every 5 days, followed by 0.1 mg/kg/day at week 4, 0.1 mg/kg every other day after 5 days and stopped at week 6. After steroid discontinuation and CR or stable PR maintained for 6 weeks, CSA is tapered over 60 days. After CSA discontinuation and no presence of recurrent GVHD, ruxolitinib is tapered off over 90 days, which is totally maintained for approximately 6 months.  **Corticosteroid treatment (corticosteroids group):**  The initial dose of methylprednisolone is 2 mg/kg/day given twice daily for at least 7 days and then reduced. The dosage of methylprednisolone in the corticosteroids group is decreased gradually after CR and tapered off over 10 weeks as the following: dosage reduced to 1 mg/kg/day to 0.6 mg/kg/day, 0.4 mg/kg/day, 0.3 mg/kg/day, 0.25 mg/kg/day, and 0.18 mg/kg every 7 days, and then 0.1 mg/kg/day at week 4, 0.1 mg/kg every other day after 5 days, and stopped at week 10. CsA was administered intravenously at a dose of 2 mg/kg twice daily, targeting minimum concentration levels of 150–250 ng/mL. The recommended duration of CsA is 6 months.  In both arms, for refractory acute GVHD, i.e., the progression of GVHD after 3 days of therapy, no improvement within 7 days, or no CR after 14 days of therapy, the second-line therapy will be started. For refractory acute GVHD or recurrent acute GVHD, basiliximab may be used as second-line therapy, and other alternative drugs included methotrexate or mesenchymal stem cells may be used at the researcher’s decision. For refractory acute GVHD, methylprednisolone is discontinued and CsA is continued in both arms. Prolonged maintenance of ruxolitinib is used in the ruxolitinib group. A standardized follow-up booklet is given to each enrolled patient for recording the dose, frequency, and administration method of the drugs. **Estimated Duration of Participation:** Subject participation is expected to average 24 months, which includes the following:   - A screening period lasting up to 28 days. - A treatment period lasting as long as the subject is benefiting from treatment. - A safety follow-up period lasting 180 days after treatment ends. - A survival follow-up period lasting until death or study withdrawal. \| \| \| **Estimated Number of Subjects:** 198 subjects. \| \| \| **Principal Coordinating Investigator:** [name] \| \| \| **Statistical Methods:**  The sample size is calculated according to the primary endpoint (ORR) of the study. Based on our published phase I study of 32 acute GVHD patients who received steroids as first-line therapy, an expected proportion of 55% for the patients treated with corticosteroids only was established. Based on our published data of patients with acute GVHD grade I–IV who received steroid-ruxolitinib (5 mg/day) as first-line therapy, the ORR was 82.05%. Patients with acute GVHD grade I were also included in the phase I analysis. Thus, an expected proportion of 75% for the patients treated with steroid-ruxolitinib (5mg/day) was established. This study is planned to detect a response difference between treatment arms at a two-sided significance level α=5% with a power of 1-β=80%. The sample size was estimated using PASS software based on the primary endpoint (ORR). Allowing a withdrawal rate of 10%, 198 patients (99/group) will be required.  Continuous data are described as median with interquartile range (IQR) or mean and standard deviation (SD) according to the normality of distribution. The categorical data are described as n (%). The ORR was calculated with its 95% confidence interval (CI) and compared by the stratified Cochran–Mantel–Haenszel test. Additionally, a logistic regression model, which included aGVHD risk (high vs. intermediate), and disease status before transplantation (CR vs. no CR) as covariates, was established to explore the association between treatment and ORR on day 28. Post-hoc subgroup analysis was performed by biomarker risk, age and GVHD grade, although these were not prespecified in the protocol. The cumulative incidence of recurrent aGVHD was analysed using the Fine and Gray test in a competing risk framework. The Kaplan–Meier method was used to estimate the ORR on day 56, OS, DFS, and FFS, and the log-rank test was used to evaluate the difference between the groups. The cumulative incidence rates of NRM and relapse were estimated using a competing risk model and compared using the Fine and Gray test. A Cox proportional hazard regression model was used for multivariable regression analysis for OS and DFS. Multivariable regression analysis was performed for NRM using the Fine–Gray proportional hazard regression for competing events. The following variables were included in the univariable analysis: primary disease, cytogenetic risk, age and gender of the donor and recipient, source of graft, treatment arm, aGVHD risk, and disease status before transplantation. Variables with P<0.1 in univariate analysis or variables known to influence the outcomes were included in the multivariable analysis. Competing events were defined as follows: for GVHD, death without the event; for relapse, death without relapse; and for NRM, relapse. Any difference for which the two-sided P<0.05 was considered statistically significant. All analyses were carried out using SPSS 22.0 software (IBM Corporation, Armonk, NY, USA) or R version 4.1.2 (www.cran.r-project.org). All statistical analyses were based on the intend to treat set. \| \| | |

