# 2. STUDY OBJECTIVES AND ENDPOINTS

| Primary Objective | Primary Endpoint |
| --- | --- |
| Compare the efficacy of ruxolitinib in combination with 1mg/kg methylprednisolone versus 2 mg/kg methylprednisolone alone in terms of overall response rate (ORR) at Day 28 in subjects with acute graft-versus-host disease (acute GVHD). | ORR at Day28, defined as the proportion of participants demonstrating a complete response (CR), or partial response (PR) |
| Secondary Objective | Secondary Endpoints |
| Compare additional response and longer-term efficacy outcomes between treatment cohorts. | Durable ORR at Day56, defined as the proportion of patients in each arm whose response on day 28 lasts until day 56 after randomization. |
|  | DOR at Month 6 for responders will be calculated. The DOR is defined from the time of the onset of response to loss of response. Subjects who died or discontinued will be censored at the  death date or the previous assessment. |
|  | Response duration, defined as the time from the first response to the first recurrence/progression of acute GVHD or additional immunosuppressants for GVHD. |
|  | NRM at Month 24, defined as the time from enrollment to death due to any causes other than hematologic disease relapse. |
|  | Cumulative incidence of relapse (CIR) at Month 24, defined as the proportion of subjects whose underlying hematologic disease relapses. |
|  | Disease-free survival (DFS) at Month 24, defined as the time from enrollment to relapse of primary disease or death from any causes, whichever occurred first. |
|  | Failure-free survival (FFS) at Month 24, defined as the time from randomization to disease relapse or progression, non-relapse mortality, or the addition of new therapy for acute GVHD. |
|  | Overall survival (OS) at Month 24, defined as the time from randomization to death due to any causes. |
| Assess the incidence and severity of adverse events (AEs) and serious adverse events. | Clinical safety data (eg, AEs, infections) will be tabulated and listed. |
| Evaluate the use and discontinuation of  corticosteroids. | Average and cumulative corticosteroid dose at Days 365; proportion of subjects who discontinue corticosteroids at Days 56 and 100. |
| Evaluate the use and discontinuation of  immunosuppressive medications. | Proportion of subjects who discontinue immunosuppressive medications at Days 365. |
| Evaluate the incidence of recurrent acute GVHD. | Incidence rate of recurrent acute GVHD through Month 12. |

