## 4.6. Duration of Treatment and Subject Participation

After signing the informed consent form (ICF), screening assessments may be completed over 1-2 days. Each subject enrolled in the study may continue to receive study treatment as long as benefit is being observed and/or treatment withdrawal criteria are not met. If the subject discontinues study treatment, the treatment period will end, and the subject will enter the follow-up period. The safety follow-up period will last 365 days, and the survival follow-up period will last until death or study withdrawal. Study participation is expected to average approximately 24 months per individual subject but may vary based on clinical outcomes.

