## 6.5. Follow-Up

### 6.5.1. Safety Follow-Up

The safety follow-up period is the interval between the EOT visit and the scheduled follow-up visit, which should occur 180 days after the EOT visit (or after the last dose of study drug if the EOT visit was not performed). Adverse events and SAEs must be reported up until at least 30 days after the last dose of study drug, the date of the follow-up visit, or until toxicities resolve, return to baseline, or are deemed irreversible, whichever is longer.

If a subject withdrew from treatment due to reasons other than disease progression, GVHD staging and grading will be repeated at the safety follow-up visit.

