### 6.5.2. Post-Treatment GVHD Follow-Up

Subjects who completed study treatment or discontinued treatment for reasons other than GVHD progression will be followed every 28 days (± 7 days) after the safety follow-up visit until any of the following occurs:

- GVHD progression.
- Initiation of a new anti-GVHD therapy.
- Relapse/recurrence of underlying hematologic disease.
- A maximum of 12 months from EOT or a maximum of 24 months from Day 1 is

reached, whichever occurs first.

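### The medication-recording window in section 7.3 closes at a safety visit whose timing is stated two ways (180 and 365 days), and at 180 days it does not clearly reach the Day-365 steroid and immunosuppressant endpoints

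*Protocol*

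**What the plan says.** Section 7.3 sets the period for the drug record: "any medication received or procedure performed within 30 days before randomization and up to the safety follow-up visit will be recorded in the eCRF". The same section also has general requirements without an end date: all concomitant medication goes into the eCRF, and dose changes are documented.

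The length of safety follow-up is given three times:
- Synopsis: "A safety follow-up period lasting 180 days after treatment ends".
- Section 6.5.1, on the follow-up visit: "which should occur 180 days after the EOT visit".
- Section 4.6: "The safety follow-up period will last 365 days".

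Section 2 places two drug-use endpoints at Day 365. One is average and cumulative corticosteroid dose. The other is "Proportion of subjects who discontinue immunosuppressive medications at Days 365".

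Two kinds of contact follow the safety visit. Under section 6.5.2, patients who completed treatment, or stopped for reasons other than GVHD progression, "will be followed every 28 days (± 7 days) after the safety follow-up visit", to at most 12 months from EOT or 24 months from Day 1. Under section 6.5.3, the remaining patients are contacted at least every 8 weeks "to assess for new GVHD therapy and survival status until death" or another end point.

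**The concern.** The endpoints are counted from randomisation, but the recording window is counted from EOT, and EOT differs by arm and by outcome. A patient who leaves study treatment early has a window that closes early. If it closes before Day 365, a steroid course restarted later, or an immunosuppressant still in use, need not be entered under the stated window.

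The later contacts do not clearly fill the gap. Section 6.5.2 specifies no drug recording. Section 6.5.3 asks about new GVHD therapy and survival, not about steroid doses or the dates on which immunosuppressants stopped.

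Cumulative steroid dose and immunosuppressant status at Day 365 could then rest on windows of different length in different patients. Reducing steroid exposure is part of the rationale in section 1.1, so this comparison matters. An analysis plan cannot recover doses that were never collected.

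**Working it through.** **Inputs (Protocol)**
- Window closes at EOT + 180 days (Synopsis, 6.5.1) or EOT + 365 days (4.6).
- Control steroid: at least 7 days at the starting dose, then a 10-week (70-day) taper after CR (5.1.2).
- Control cyclosporine: 6 months, taken as 180–183 days (5.1.2).
- Early failure: criteria are met between Day 3 and Day 14 (5.1.1.1). A need for additional systemic therapy requires withdrawal from study treatment (5.4.1), which ends the treatment period (5.4).
- Ruxolitinib: about 6 months in total, or the sum of the listed steps (5.1.1.1).
- Study drugs: section 7.4.2.2 names ruxolitinib and the corticosteroid only, whereas section 5.1.2, under the Study Drugs heading, also includes cyclosporine.

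**Formula.** Closing day = EOT day + 180, and shortfall = 365 − closing day. Day 365 is reached only if EOT is on or after 365 − 180 = Day 185. One-day differences in numbering are ignored.

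**Under the 180-day rule**

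| Patient | EOT day | Window closes | Days short of 365 |
| --- | --- | --- | --- |
| Control completer, steroid stopped at week 10 from start | 70 | 250 | 115 |
| Control completer, 7 + 70 | 77 | 257 | 108 |
| Control completer, CR at Day 14, then 70 | 84 | 264 | 101 |
| Control completer, if cyclosporine sets EOT | 180–183 | 360–363 | 2–5 |
| Early failure, Day 3 | 3 | 183 | 182 |
| Early failure, Day 14 | 14 | 194 | 171 |
| Ruxolitinib completer, about 6 months | 180 | 360 | 5 |
| Ruxolitinib completer, 42 + 42 + 60 + 90 | 234 | 414 | 0 |
| Ruxolitinib completer, 7 + 42 + 42 + 60 + 90 | 241 | 421 | 0 |

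As a share of the year, 101–115 days is 28–32% and 171–182 days is 47–50%.

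**Under the 365-day rule.** Control completers close at Day 435–449 (70 + 365 to 84 + 365) and early failures at Day 368–379 (3 + 365 to 14 + 365). Day 365 is covered. However, the 6.5.2 visits start after the safety visit and end at most 12 months from EOT, so their period is 365 − 365 = 0 days. With 180 days it is 365 − 180 = 185 days, which is workable.

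Each stated length therefore leaves one part of the protocol unsatisfied: 180 days does not secure the drug endpoints, and 365 days empties section 6.5.2.

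**The case against.** A reader might infer that Day-365 drug data are simply not collected in control patients and that the control arm's cumulative dose will be undercounted. The documents do not support that, for five reasons.

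- **Other recording text.** The remaining sentences of 7.3 have no closing date, and the Synopsis gives every patient a booklet for drug doses. Appendix A has rows for steroid dose monitoring and concomitant medication, with columns to +36 months. Its marks cannot be read in the text available here. If +12 months is marked, steroid dosing is scheduled there. That would ease the practical risk but contradict the window in 7.3.
- **What sets EOT.** If cyclosporine counts as study treatment, control completers are 2–5 days short, much like ruxolitinib completers on the six-month reading, and the difference between arms among completers nearly disappears. Both readings have support in the text.
- **Planned courses are inside the record.** A control completer's steroid (Day 70–84) and planned cyclosporine (Day 180–183) both end before Day 250. Only later restarts or prolonged use could be missed.
- **Some later use is picked up.** Completers enter 6.5.2 before 6.5.3, the start of new GVHD therapy is asked about, and re-treatment under 6.4 repeats the EOT and safety visits, which reopens the record.
- **Early failure occurs in both arms.** Section 5.1.1.1 allows ruxolitinib to continue in refractory disease, so EOT in that arm may be later. The Synopsis also continues cyclosporine in both arms, so the control figure too rests on 5.4.1 fixing EOT at withdrawal.

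All of this limits the size and certainty of the point. It does not remove it: no legible later contact asks for steroid dose or immunosuppressant stop dates, and 7.3 states an explicit end that sites may follow.

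**Conclusion.** The point holds as a conflict within the protocol. The 180-day and 365-day statements cannot both stand. Under the 180-day rule the explicit window in 7.3 does not clearly require recording to Day 365 for anyone with EOT before Day 185.

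The shortfall is largest and least dependent on the study-drug question for early failures (171–182 days), provided withdrawal under 5.4.1 sets EOT. For control completers it ranges from 2–5 days to 101–115 days, depending on whether cyclosporine counts as study drug. For ruxolitinib completers it is 0 to about 5 days.

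These are calendar days outside a required window, not amounts of lost drug exposure. No direction or size of bias can be derived from the documents. The matter concerns two secondary endpoints, not the primary analysis, and is worth correcting because the information is hard to reconstruct later.

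**What to change.** 1. State one safety follow-up length consistently in the Synopsis, 4.6 and 6.5.1. A 180-day length leaves 6.5.2 workable as written; a 365-day length would leave its visits no period to occupy.
2. In 7.3, require corticosteroids and immunosuppressants (drug, dose, start and stop dates) to be recorded to Day 365 from randomisation for every randomised patient, whatever the EOT date. Collect them at the contacts already planned in 6.5.2 and 6.5.3, and make the Appendix A rows agree.
3. Say whether cyclosporine counts as study drug when EOT is determined, so that the window can be read in one way.

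The cost is protocol wording and some additional eCRF entries. No new visits are needed, and the start of the 6.5.2 visits can stay where it is.
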